## Background

Community-led interventions that systematically and strategically implement evidence-based programs have been shown to be effective in producing population-level behaviour change, including reduced alcohol and drug use. Australian guidelines recommend that adolescents should not consume alcohol before they are 18 years but 44% do, with 34% reporting use in the last 30 days [1]. Community interventions such as the “Communities That Care” prevention framework have the potential to reduce these adolescent alcohol consumption (CTC; [2–4]. The CTC framework can be used to mobilise community stakeholders and organise them to work strategically to prevent the development of harmful behaviour patterns. Communities are supported to utilise local data to identify priorities and then to plan the implementation of interventions that have been found to be effective in previous evaluations.

Large community trials in the United States of America (USA) reveal that CTC can increase community implementation of evidence-based prevention interventions and reduce health-risk behaviour patterns among teenagers, resulting in reductions of between 15% - 25% in the prevalence of youth problems [2, 4]. Economic evaluations also indicate that CTC is worthwhile investment. Conservative estimates suggest CTC can produce a return on investment of approximately US$10.23 for every dollar [5, 6]. Over ten years, pilot work developing CTC in Australia has facilitated recruitment and training of community coalitions to plan and implement evidence-based programs. This work has demonstrated feasibility of CTC in Australia. Pilot studies have shown the CTC approach has been successfully implemented with fidelity and has been associated with reductions in teenage alcohol and drug use in line with those achieved in the USA (i.e. 15%) [7]. This study will employ a Type II translational randomised control trial to evaluate the effectiveness of CTC in Australia.

The primary outcome will be the proportion of secondary school age adolescents who use alcohol before the Australian legal purchasing age of 18 years. Based on pilot work done in Australia and CTC trial work done in the USA, we hypothesise that: compared to control communities, participants in intervention communities will maintain at least a 15% lower rate of frequent (last 30 days) youth alcohol use throughout the secondary school age period (primary outcome).

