### Sample size

Previous data indicate the intraclass correlation coefficients (ICC) for alcohol consumption in the last 30 days at community and school levels were .01 and .05, respectively. We calculated the required sample with power 0.8, type I error 0.05 and design effects based on clustering effect (ICC) at community, school and classroom clustering ranging from 0.1 to 0.01. Recent Australian secondary school survey data [10] indicate rates of alcohol use in the past month were 22% in grade 8 (average age 14) and 48% in grade 10 (age 16) (combined average 35%). Assuming 65% of parents consent to their child participating, we will request informed consent from 5400 to recruit 3500 students in 2017 (wave 1). These cohorts will be resurveyed at two time points after the intervention is delivered. Assuming an 80% retention rate, the hypothesised 15% reduction can be detected with 2800 participants in the longitudinal analyses. The research team will work with communities and relevant stakeholders to recruit schools for the study. Primary outcome data will be collected in the school setting using the CTC youth survey.

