### Statistical analyses

Intention-to-treat analyses will be employed. To account for within-individual variation we will employ repeated measures models with split-plot in time design matrix with binary outcome and logit link. Model parameters will be estimated using generalised estimating equations (GEEs) accounting for correlation within participants with an exchangeable working correlation matrix. For continuous secondary outcomes, GEEs with a Gaussian distribution and identity link will be implemented.

To assess the impact of the intervention on primary and secondary outcomes, time by treatment interactions will be examined in a model that includes the fixed categorical effects of assessment time, group indicator and treatment by group interaction. Trend effects due to staggered rollout of the intervention will be assed using models with a fixed effect categorical factor for year of treatment.

Clustering effects for schools and communities will be evaluated by calculating ICC and, if necessary, a series of (generalised) linear mixed models accounting for *clustering* (within participant/class/school/community). Analysts will not be blind to the communities that have been allocated to either intervention or control.

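### The primary logit GEE leaves out the randomised unit, and the only remedy named is an ICC-triggered mixed model whose coefficient would not directly express the 15% lower population rate

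*Protocol article*

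**What the plan says.** The hypothesis in Background is about a population rate: intervention communities are to "maintain at least a 15% lower rate of frequent (last 30 days) youth alcohol use throughout the secondary school age period".

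Statistical analyses then specifies, for the binary outcome, "repeated measures models with split-plot in time design matrix with binary outcome and logit link". Estimation is described as follows: "Model parameters will be estimated using generalised estimating equations (GEEs) accounting for correlation within participants with an exchangeable working correlation matrix". The treatment effect is read from the interaction: "time by treatment interactions will be examined in a model that includes the fixed categorical effects of assessment time, group indicator", plus the interaction term itself.

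Clustering above the participant appears later in that section and is conditional: "Clustering effects for schools and communities will be evaluated by calculating ICC and, if necessary, a series of (generalised) linear mixed models accounting for" clustering, with the levels given as "within participant/class/school/community". The section gives no ICC value that triggers this step. It does not say which model carries the primary result, or on what scale the 15% is judged. It also says that the analysts will know which communities are in which arm.

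Sample size reports that earlier ICCs for this outcome "at community and school levels were .01 and .05, respectively". Random allocation describes 28 communities, 14 per arm.

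**The concern.** There are two problems, and solving the first by the route the plan names creates the second.

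1. The GEE as described treats participants as the independent units. Communities were randomised, so its standard errors omit the variation between the units that were allocated.
2. The only remedy named is a set of mixed models. With a logit link, the GEE coefficient compares population proportions on the odds scale. A random-intercept model with a participant term compares the odds for a given individual, and its coefficient lies further from zero on the same data. The hypothesis concerns a population rate, so the GEE coefficient matches it directly and the conditional one does not.

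The numerical meaning of the primary effect could therefore depend on an ICC check with no stated threshold, made by analysts who are not blinded. If a conditional odds ratio were then read against the 15% target as a population effect, a true reduction below 15% could appear to meet it. The point applies to binary outcomes. With an identity link, as for the continuous secondary outcomes, the marginal and conditional coefficients coincide.

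**Working it through.** **Inputs from the protocol article.** Past-month use is 22% in grade 8 and 48% in grade 10 (Sample size); (22 + 48)/2 = 35%, as stated there. The target is a 15% lower rate (Background): 0.85 × 35% = 29.75%. ICCs are .01 for community and .05 for school (Sample size). There are 28 communities and 2800 participants in the longitudinal analysis.

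**Assumed input.** The within-person correlation of the repeated yes/no item is not given. I use 0.2 to 0.5 and show the range. The arms are taken as equal at baseline, so the follow-up contrast equals the interaction.

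**Step 1: what the participant-only GEE leaves out.** Participants per community: 2800/28 = 100. Design effect for a single-wave contrast from the community ICC alone: 1 + (100 − 1) × 0.01 = 1.99. True standard errors would be about √1.99 = 1.41 times those that ignore community. For change from baseline the factor is smaller if community differences are stable over time.

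**Step 2: marginal odds ratio.** (0.2975/0.7025)/(0.35/0.65) = 0.4235/0.5385 = 0.786; log odds ratio −0.240.

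**Step 3: conditional odds ratio for the same two rates.** In a random-intercept logistic model the population rate is p = ∫ expit(a + σz) φ(z) dz. I chose σ so that the within-person correlation, (E[π²] − p²)/(p(1 − p)) with π = expit(a + σz), equals the assumed value at p = 0.35. I then solved for the intercept a at 35% and at 29.75% by Gauss-Hermite quadrature. The conditional odds ratio is exp(a at 29.75% − a at 35%).

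**Step 4: the misreading.** Apply the conditional odds ratio to the population odds 0.35/0.65 and convert back to a rate. At correlation 0.2: 0.742 × 0.5385 = 0.3994; 0.3994/1.3994 = 28.54%; (35 − 28.54)/35 = 18.5%.

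**Step 5: the reverse.** Set the conditional odds ratio to 0.786 and integrate to find the true population reduction.

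| Assumed correlation | σ | a at 35% | a at 29.75% | Conditional OR | Ratio of log ORs | Apparent reduction if misread | True reduction when conditional OR is 0.786 |
|---|---|---|---|---|---|---|---|
| 0.2 | 1.15 | −0.780 | −1.079 | 0.742 | 1.24 | 18.5% | 12% |
| 0.3 | 1.58 | −0.893 | −1.234 | 0.711 | 1.42 | 20.9% | 11% |
| 0.4 | 2.09 | −1.044 | −1.441 | 0.672 | 1.65 | 24.1% | 9% |
| 0.5 | 2.74 | −1.253 | −1.730 | 0.621 | 1.98 | 28.4% | 8% |

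**Step 6: school and community effects only.** The total ICC is .01 + .05 = .06. Treated as a correlation of the binary item, it gives σ 0.54, conditional OR 0.775, log-OR ratio 1.06 and an apparent reduction of 15.9%. Treated as an ICC on the latent logistic scale, it gives conditional OR 0.778 and 15.6%. Both are about 16%, so the participant term causes nearly all of the shift.

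**The case against.** A reader might infer that the plan swaps the GEE for a mixed model and will therefore overstate the intervention's effect by the amounts in the table. The article does not support that.

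- It commits to GEE first and never says that the mixed models take over the primary result. A supplementary check is an equally natural reading.
- The apparent 18.5% to 28.4% needs two things the article does not contain: a within-person correlation of 0.2 to 0.5, and an analyst who applies a conditional odds ratio to the population odds. No reporting scale is named, and a mixed model can be averaged back to population proportions.
- A reader might also infer that coefficients will be compared across the series of mixed models to judge whether clustering matters. The article proposes no such comparison; clustering is to be judged by the ICC.
- The change of scale does little to the test. With arms equal at baseline, no effect is zero on both scales, and coefficient and standard error grow together.
- Post-estimation steps and reporting scale are commonly left to the statistical analysis plan.

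All of this stands and limits the point to how the effect size is read. It does not remove the point, because the article itself fixes the structure. Followed as written, the plan leads either to a GEE that omits the randomised unit or to a data-triggered move to models with a different coefficient. That is a poor choice stated in the text, not a missing detail.

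**Conclusion.** The point holds in a limited form. The GEE described accounts only for within-participant correlation in a community-randomised trial, and the one remedy named is an optional step into logistic mixed models with a participant level. Whether those models replace or supplement the GEE is not stated. If they replace it, the primary coefficient becomes participant-conditional and no longer maps directly to the 15% lower rate.

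The size is illustrative. For a true 15% reduction from 35%, the odds ratio moves from 0.786 to between 0.742 and 0.621 under the assumed correlation of 0.2 to 0.5. With only the ICCs the article reports, the misread reduction would be about 16%, which is negligible. The consequence of the scale change is for interpreting the effect, not for the false-positive rate. Leaving community out of the GEE is the part that does affect standard errors.

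**What to change.** For the binary primary outcome, remove the ICC-triggered step. State that the primary analysis is a population-averaged logit GEE with community as the independent cluster and a robust variance corrected for the small number of clusters (28 communities). If a logistic mixed model is also fitted, label it supplementary, and judge the 15% target only on proportions standardised over the random effects, not on the conditional odds ratio.

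This takes one or two sentences, one routine post-estimation step if the mixed model is kept, and no new data. Intervals will be wider than those from the participant-only GEE, because that model leaves out community variation; the small-sample correction itself adds little.

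### The conditional mixed model names no cluster-by-wave term, so if fitted as nested random intercepts it leaves the time-by-treatment test resting on participant-level error

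*Protocol article*

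**What the plan says.** All of the following is in the protocol article.

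- **Tested effect** (Statistical analyses): "time by treatment interactions will be examined in a model that includes the fixed categorical effects of assessment time", together with group. There are three waves, one before and two after the intervention (Participants and research eligibility), so a categorical test has 2 degrees of freedom and a single-wave contrast has 1.
- **Main estimator** (Statistical analyses): GEE with an exchangeable correlation within participants.
- **Clustering** (Statistical analyses): "Clustering effects for schools and communities will be evaluated by calculating ICC" and then, "if necessary, a series of (generalised) linear mixed models accounting for" clustering "within participant/class/school/community".
- **Randomisation** (Random allocation): 28 areas in 14 matched pairs, one of each pair to each arm.
- **ICCs** (Sample size): "at community and school levels were .01 and .05, respectively", for drinking in the last 30 days. No between-wave correlation of cluster effects is given, and no within-person correlation.
- **Waves and grades** (Fig. 1 legend): wave 1 may be Years 8 and 10 or Years 9 and 11. The final wave is Year 11 and one year after school.

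**The concern.** The effect of interest is a difference in change. A community or school effect that is the same at every wave adds equally to the before and after measurements and drops out of the change. What then governs the error of the test is how far communities and schools drift apart between waves. The listed levels contain no term for that drift.

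The trigger has the same weakness. An ICC of drinking at one wave measures clustering of level, not of change. It can be small or large without saying how much change is clustered.

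An analyst could therefore calculate the ICC, move to the multilevel model, believe clustering is handled, and still report intervals that are too narrow for a 28-community trial. This differs from the participant-only GEE in the same section: moving from that GEE to the listed mixed model would not in itself cure it.

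**Working it through.** **Inputs from the protocol.** The recruitment chain reproduces: 5400 × 0.65 = 3510, and 3500 × 0.80 = 2800. Then 2800 / 28 = 100 pupils per community and, with two schools each, 50 per school. ICCs are ρc = .01 (community) and ρs = .05 (school). Type I error is 0.05, taken as two-sided.

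**Assumptions, not in the protocol.** Between-wave correlation of cluster effects, κ: 1.0 to 0.6. Within-person correlation, r: about .36.

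**Formula.** Take total variance 1 and ρ = ρc + ρs. In a linear, balanced model the participant part of a two-wave change has variance 2(1−ρ)(1−r). The community and school parts have 2(1−κ)ρc and 2(1−κ)ρs, shared by 100 and 50 pupils. A model with intercepts only treats all of it as independent between pupils. True variance divided by the variance the model sees is

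D = [(1−ρ)(1−r) + (1−κ)(100ρc + 50ρs)] / [(1−ρ)(1−r) + (1−κ)ρ].

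Type I error is 2{1 − Φ(1.96/√D)} for 1 df and exp{−5.991/(2D)} for 2 df.

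**Example, κ = 0.9.** (1−ρ)(1−r) = 0.94 × 0.64 = 0.6016. Then D = (0.6016 + 0.1 × 3.5) / (0.6016 + 0.1 × 0.06) = 0.9516 / 0.6076 = 1.57. Type I error is 12% (1 df) and 15% (2 df).

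| κ | .01 plus .05: D; 1 df, 2 df | .05 as total within school: D; 1 df, 2 df | community .01 only: D; 1 df, 2 df |
|---|---|---|---|
| 1.0 | 1.00; 5%, 5% | 1.00; 5%, 5% | 1.00; 5%, 5% |
| 0.9 | 1.57; 12%, 15% | 1.48; 11%, 13% | 1.16; 7%, 7% |
| 0.8 | 2.12; 18%, 24% | 1.95; 16%, 22% | 1.31; 9%, 10% |
| 0.6 | 3.20; 27%, 39% | 2.88; 25%, 35% | 1.62; 12%, 16% |

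**Other values of r.** With both ICCs and κ = 0.9, r = 0.3 gives 11% and 14%, and r = 0.6 gives 16% and 21%. With the community ICC alone, r = .36 and κ = 0.5, the rates are 14% and 18%.

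**Simulation.** Binary outcome, no effect, 28 communities × 2 schools × 50 pupils × 3 waves, complete data. At κ = 1.0, 0.9, 0.8 and 0.6 the participant-level change test rejected in 5, 11, 18 and 28% of trials (1 df) and 5, 13, 25 and 41% (2 df). With .05 as the total within-school ICC, the last three were 10, 15 and 24% (1 df) and 12, 21 and 34% (2 df). A t-test on the 28 community mean changes (26 df) stayed at about 5% throughout.

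**Could clusters drift?** The Fig. 1 legend gives one possible route. Past-month use is 22% in grade 8 and 48% in grade 10, about 13 points per grade. Suppose 25% of communities start one grade later, unrelated to arm. The community variance of change is 0.13² × 0.25 × 0.75 = 0.0032. Participant change variance is about 2 × 0.35 × 0.65 × (1 − 0.34) = 0.30, with .34 assumed. Then D ≈ 1 + 100 × 0.0032 / 0.30 ≈ 2.1, or about 17% (1 df). Simulation gave 12, 17 and 21% when 10, 25 and 50% of communities start later. The legend does not say that the start grade will differ between communities, so this is only an illustration.

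**The case against.** The strongest reply is that the article names grouping levels, not random-effect terms. A model with community-by-wave effects also accounts for clustering within community, and such terms are often left to an analysis plan, which is not shown. This stands to the extent that nobody can say the plan prescribes intercepts only. It does not remove the point. The levels are written out, the one that governs the tested contrast is not among them, and the conventional fit of that list gives the problem shown.

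A reader might go further and infer that the primary test has a type I error of 14–40%. The document does not support that. Those rates need an assumed κ between about 0.9 and 0.6 and the 2-df test. With stable clusters the rate is 5%.

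Three further objections hold in part:

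- Cancellation is exact only for a linear, balanced model with fixed membership. With a logit link and the planned 80% retention it is approximate.
- Class is a listed level. If class effects were new at each wave they would not cancel and would absorb part of the drift. A rough linear check of the 2-df test lowers about 14, 24 and 40% (κ = 0.9, 0.8, 0.6) to about 9, 12 and 16% with two classes per school, or 12, 17 and 26% with four. The number of classes is assumed.
- A reader might also infer that pupils change class between waves. The article does not say so. It supports only that the older cohort has left school by the final wave and so cannot be assigned to a class then.

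**Conclusion.** The concern holds in conditional form. The tested effect is a change. The only clustered model is conditional on an ICC check that need not reflect clustering of change, and no cluster-by-wave term is named. Fitted as nested random intercepts, it would test the intervention largely against participant-level variation.

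Type I error would then run from about 5% with perfectly stable clusters, through 11–14% and 18–25%, to 28–41% as κ falls from 1.0 to 0.9, 0.8 and 0.6. Each range runs from the 1-df to the 2-df test. These figures move by several points with r and with how the school ICC is read, and fall to about 6–20% if only the community ICC applies or if wave-specific class effects are modelled with few classes per school. The direction is secure. The size is not fixed by the document, because it gives neither κ nor r.

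**What to change.** Make the clustered analysis unconditional rather than dependent on a calculated ICC, and fix school and community at wave-1 membership. Then choose one of two routes and state it:

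1. A mixed model with community-by-wave and school-by-wave random effects in addition to community, school and participant, with degrees of freedom based on the number of communities.
2. An analysis of the 28 community-level changes that respects the 14 matched pairs (a paired analysis has 13 degrees of freedom).

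Do not rely on class as a fixed nested level, since the older cohort is out of school at the final wave.

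The change is a sentence or two of analysis wording. The price is wider confidence intervals. Route 1 is also somewhat harder to fit, since several variance components must be estimated from 28 communities with a community ICC near .01. Route 2 avoids that difficulty.

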### Sensitivity analysis

Primary analyses assume the missing data are missing at random (MAR). It is thus important to assess the sensitivity of analysis under the MAR assumption to the not missing at random (NMAR) assumption. We will investigate various scenarios of non-ignorable missing data mechanisms through a sensitivity analysis based on a mixture modelling approach. Missing data will be imputed under MAR assumption first, and parameter estimates for each imputed data set will be obtained [20].

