### Secondary outcome analyses

Per-protocol and subgroup analyses will be performed. Depending on sample size, subgroup analyses will examine differential effects by age, gender, community, rural areas, socio-economic status, State, and the extent of implementation and fidelity to the CTC process. Using (generalised) structural equation models, analysis of whether effects intervention processes on multiple outcomes (e.g. alcohol and drug use; violence; school completion) are mediated by changes in patterns of adolescent alcohol use will be assessed, after adjusting for other risk factors. Specified intervention mechanisms examined will include: percentage of outlets selling alcohol to perceived minors, reported exposure to brief communication resources; reduced perceptions of alcohol availability from different sources; and less favourable peer, family and community attitudes to alcohol. In addition, individual-level mediation analyses will be used to explore how any observed intervention effects on knowledge, attitudes, intention and skills account for any observed differences in reported alcohol consumption over the last 30 days.

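### Analysts who know the arms decide, after seeing the ICC, whether the primary analysis accounts for school and community clustering

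*Protocol article*

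**What the plan says.** The Statistical analyses section of the protocol article fixes part of the primary analysis: "Intention-to-treat analyses will be employed", with a binary outcome, a logit link and GEE "accounting for correlation within participants with an exchangeable working correlation matrix". This base model handles repeated measures on one participant and nothing above that level.

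Clustering by school and community "will be evaluated by calculating ICC and, if necessary, a series of (generalised) linear mixed models". No ICC threshold is given, and no member of the series is named as the final primary model. The section then closes with a positive statement about masking: "Analysts will not be blind to the communities that have been allocated to either intervention or control". It gives no reason.

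Other sections bear on this:
- Random allocation: communities are the randomised units, 14 per arm, in matched pairs.
- Sample size: previous data put the ICC for the primary outcome at .01 (community) and .05 (school).
- Sensitivity analysis: the primary analysis assumes missing at random. Beyond that, "We will investigate various scenarios of non-ignorable missing data mechanisms".
- Secondary outcome analyses: "Depending on sample size, subgroup analyses will examine differential effects", by a list of named factors.

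**The concern.** Unblinded analysis is common and is not a fault in itself. The difficulty is its combination with an unfixed primary model. The article randomises communities and already reports non-zero ICCs, yet makes adjustment for clusters conditional on a judgement made with the data in hand. A community ICC of .01 may look negligible to an analyst, although with 100 participants per community it roughly doubles the variance.

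The choice can change the p-value. It can also change the estimate, because the GEE gives a population-averaged odds ratio and a logit mixed model gives a cluster-specific one. An analyst who knows the arms can see which option favours the intervention. The primary outcome is a self-reported yes/no item, and the article describes no masking of participants or community staff, so masking the analysis is a protection that is still available.

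**Working it through.** The plan gives no figure for the effect of analyst blinding, so there is none to reproduce. What can be sized is the open choice itself: how far the primary test moves if clusters are ignored.

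**Inputs**
- Analysed sample 2800 (Sample size); 3500 × 0.80 = 2800 reproduces.
- 28 communities, 14 per arm (Random allocation), so 2800 / 28 = 100 per community.
- Two schools per community (Participants and research eligibility), so 100 / 2 = 50 per school.
- ICC .01 community and .05 school; type I error 0.05 (Sample size). Sidedness is not stated; two-sided is assumed.
- Equal cluster sizes are assumed, and class-level clustering is left out.

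**End-of-follow-up comparison**

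Let c be the community component and s the additional school component.

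DE = 1 + 49 × (c + s) + 50 × c

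True type I error if clusters are ignored = 2 × [1 − Φ(1.96 / √DE)]

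The article does not say whether the school ICC includes the community component, so both readings are shown, with community clustering alone as the lower case.

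| Reading | DE | Type I error, formula | Simulation |
|---|---|---|---|
| Community .01 only | 1 + 0.49 + 0.50 = 1.99 | 0.165 | 0.162 |
| School .05 including community .01 | 1 + 2.45 + 0.50 = 3.95 | 0.324 | 0.324 |
| Additive, .01 + .05 | 1 + 2.94 + 0.50 = 4.44 | 0.352 | 0.357 |

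The simulation used 10,000 null data sets of 28 communities × 2 schools × 50 students. Community-level t-tests on the same data sets, unpaired or paired, had type I error between 0.046 and 0.055.

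**Planned time-by-treatment contrast**

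The plan tests change over time by arm, and stable cluster effects cancel from a change. Let r be the within-person correlation and a the correlation of a cluster's effect between two waves. The article gives neither; r from 0.3 to 0.5 is assumed.

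V = 2 × {1 − [r × (1 − c − s) + a × (c + s)]}

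DE = 1 + 49 × 2(1 − a)(c + s) / V + 50 × 2(1 − a)c / V

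For example, c = .01, s = .04, r = 0.5 and a = 0.8 give V = 2 × (1 − 0.515) = 0.97, DE = 1 + 49 × 0.02 / 0.97 + 50 × 0.004 / 0.97 = 2.22, and type I error 0.188.

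| a | Type I error over the three ICC readings, r 0.3 to 0.5 |
|---|---|
| 1 (fully stable) | 0.05 |
| 0.8 | 0.08 to 0.21 |
| 0.5 | 0.13 to 0.35 |
| 0 | 0.21 to 0.47 |

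The choice is therefore immaterial only if cluster effects hardly change between waves.

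**The case against.** The strongest reply is that the article discloses its blinding status openly and contradicts nothing in doing so. The ICC that triggers the cluster model does not depend on which arm is which. The inflation above is the same whether or not the analyst knows the arms. Coding the arms would not remove the choice either: a two-sided p-value is unchanged when two labels are swapped, so a masked analyst could still fit both models and keep the smaller one. An SAP that is not shown may name the model.

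Most of this stands, and it shapes the point. The figures measure the clustering choice and say nothing about unblinding. Coding alone is not enough; the model must also be named. What does not stand is the appeal to an unseen SAP, because the article does not stay silent here. It states a conditional rule without a criterion, and it states that those applying the rule will know the arms. A trigger without a threshold is a judgement, however neutral the statistic behind it.

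Masking also has practical limits. The model with a factor for year of treatment could reveal the arm if control communities have no such year. Exposure to the programme's resources could reveal it too. The article says that intervention sites can be obtained from the research team, so community names must be coded as well, and the pair structure may still help someone identify a community. These limits affect the order of the work. They do not prevent masking of the primary analysis, because both arms have the same three-wave survey.

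**Conclusion.** The point holds in a narrow form. Unblinded analysts are given an unfixed choice, made after seeing the data, about clustering in the primary analysis. For an end-of-follow-up comparison, ignoring clusters would give a type I error of about 0.16 to 0.35 instead of 0.05. For the planned interaction it would be 0.05 or more, by an amount the article does not let one determine. This rests on 100 per community, 50 per school, equal clusters, a two-sided test and the stated ICCs.

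A reader might infer more, and the article does not support it:
- That the open missing-data scenarios and the subgroups can steer the primary result. Missing at random is fixed for the primary analysis, the other scenarios are sensitivity work, and the subgroup factors are named and placed under secondary analyses. Their detail is commonly left to an SAP.
- That 0.32, or any other figure above, is the false-positive rate caused by unblinding. No such rate can be derived.
- That nothing in the trial is blinded. The Random allocation section describes the independent statistician as blind to the allocation sequence.

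This is a worthwhile and cheap improvement. It does not show that the trial's result will be biased.

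**What to change.** Replace the sentence on analyst blinding with:

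> The primary model will account for clustering by community and school and will be fixed before outcome data are compared by arm. Analysts will work on data with coded arms and communities (pair, school and class structure kept) until the primary model, covariates and imputation model are signed off; a person not involved in the analysis holds the key.

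Remove the conditional wording on clustering from the same section, so that the two statements agree. Run the year-of-treatment rollout, exposure, fidelity and mediation analyses only after the key is released, since they can reveal the arm.

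Naming the model removes the choice sized above. Coding protects the remaining decisions on covariates and imputation. The cost is a recoding step and a short delay to the deferred analyses. Someone must be appointed to hold the key; the article does not say that the statistician who made the allocation keeps one or has a continuing role.
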